### Statistical considerations

A target of 30 complete participant datasets has been set based on an assessment of anticipated patient numbers, recruitment and attrition rates, together with a power calculation of the number of datasets required to indicate a statistically significant variation in SPECT image intensity. A clinically significant difference would be a reduction of 20% from baseline to a follow-up imaging study [5]. In order to detect a conservative estimate of a 10% reduction, where the measurement error is 20% we would require a sample size of 33 (using a paired t-test with alpha = 0.05 and power = 80%; detecting 10.5% with 30 patients which is sufficient). With an anticipated 20% non-completion/attrition rate, allowance will be made for up to 40 recruited patients. Given the intensive data analysis required per patient dataset in this study, 30 datasets represents an upper-limit in terms of manageability.

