### Study hypotheses

An assessment of changes in total kidney function (using GFR measurement), regional kidney functional change (using SPECT imaging) and their correlation with radiotherapy dose delivery is within the means of currently available imaging, therapy and computational technology. The hypotheses being tested in RAPRASI are:

– Temporal variations in SPECT images of the kidneys correlate with patterns of radiation dose delivery in the kidneys.

– Models of kidney response developed from SPECT-response studies can be used to predict changes in kidney function as a result of radiation therapy.

The principal aim of RAPRASI is to obtain a better understating of kidney response when a patient is receiving radiotherapy for an upper-abdominal cancer. This will involve monitoring the spatial and temporal changes in kidney function for correlation with delivered three-dimensional radiation dose distribution. A more precise dose-volume response model for kidney will not only improve our current understanding but may permit further optimisation of radiation therapy techniques for upper-abdominal tumours.

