**Figure 2 F2:**
[figure not shown]
Diagram of the co-registration method.

This subsequent analysis of co-registered dose and image data will be undertaken in several ways:

i. Methods will be developed to assess dose-response correlations as a function of spatial position across each kidney (sampled at varying resolutions). Kidney volumes will be uniformly divided into regions on the three-dimensional (3D) grid defining image and spatially-registered radiation dose. t-tests and Wilcoxon signed-rank tests will be undertaken to determine regions with significantly different mean SPECT-signal intensities between time-points for each study participant. Mixed modelling with repeated measures (and random subject effect) will be conducted across all participant sets to examine the correlation of local radiation dose with SPECT signal changes, generating a map of dose-response change across all kidney volumes. Given a significant correlation, this will be extended to incorporate any revealed patterns of co-morbidity or adjuvant therapy as categorical variables.

ii. Dose-response correlations will then be examined according to structural and functional regions. Analysis i. will be repeated, but with regions defined according to kidney structure, with medulla, renal artery and cortex regions treated independently. This will also involve cross-correlation between these regions to examine inter-play that is likely to arise due to the influence of radiation effects on vascular structures.

iii. Spatio-temporal mathematical models of functional kidney dose-response will be implemented to relate regional kidney irradiation to the primary measure of total kidney function, GFR. These models, including percolation theory [25] and the critical functioning volume model of Rutkowska et al [26], will utilise the 3D radiotherapy dose distribution (both across each kidney and across individual functional regions) to fit model parameters using maximum likelihood estimation (MLE) methods. The statistical assessment of fitting will be made by assessment of parameter confidence intervals, and by undertaking an F-test of the residual sums-of-squares from MLE against that from MLE for a simple linear (single-parameter) dose-response model.

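### The stated 80% power belongs to a patient-level paired t-test that is not among the article's listed analyses, and it does not carry over to the dose-correlation model that tests hypothesis 1

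*Protocol article*

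**What the plan says.** **Sample size (Protocol article, Statistical considerations).** The stated aim is a "power calculation of the number of datasets required to indicate a statistically significant variation in SPECT image intensity". The effect is a 10% reduction from baseline, and "where the measurement error is 20% we would require a sample size of 33", with the test and error rates given as "using a paired t-test with alpha = 0.05 and power = 80" per cent. The target of 30 is then accepted on the ground of "detecting 10.5% with 30 patients which is sufficient". Patients are the unit throughout. Feasibility (expected numbers, recruitment, attrition and the analysis workload) is given as a further basis for 30.

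**Hypothesis 1 (Study hypotheses).** "Temporal variations in SPECT images of the kidneys correlate with patterns of radiation dose delivery in the kidneys". This is a statement about dose, not about an average fall.

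**Analyses (Data analysis, items i to iv).** Item i uses t-tests and Wilcoxon signed-rank tests to find regions with "significantly different mean SPECT-signal intensities between time-points for each study participant". It then fits a repeated-measures mixed model over all participants to "examine the correlation of local radiation dose with SPECT signal changes". Item ii repeats item i by anatomical structure. Items iii and iv fit dose-response models by maximum likelihood.

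**The concern.** A power figure is useful only if it refers to a test that the study will perform. Here the sizing section and the analysis section have different units. The first counts patients. The comparisons of time points in the second count observations inside one patient's kidney, so recruiting 10 or 30 patients leaves the power of each such test unchanged.

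The analysis that does pool patients asks another question: whether regional change follows regional dose. A mean fall in SPECT intensity could occur with no relation to dose, so power to detect the fall is not power to detect the correlation.

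Two things are at stake. The sample size is called sufficient on a figure that supports no listed analysis. And the test of hypothesis 1 has no stated sensitivity, although its result decides what follows: item i brings in co-morbidity and adjuvant therapy only if the correlation is significant.

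**Working it through.** **1. Reproducing the plan's figure.** Inputs from Statistical considerations: reduction δ = 10%, measurement error 20%, α = 0.05, power 80%. The article does not say whether the test is two-sided, or whether 20% is the SD of the paired difference. Taking both as true:

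- Standardised effect: δ/SD = 10/20 = 0.5.
- Normal approximation: n = ((1.960 + 0.842) × 20/10)² = 31.4.
- Exact noncentral t with n − 1 degrees of freedom and noncentrality 0.5√n: n = 33.4. Power is 79.5% at 33 and 80.8% at 34.
- Detectable difference at n = 30 with 80% power: 10.58%. Power at exactly 10.5% (standardised 0.525): 79.4%.

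The stated 33 and 10.5% are therefore reproduced to within rounding. Other readings do not give them: a one-sided test needs 26.1 patients, and 20% taken as the error of each scan (SD of difference 20√2 = 28.3%) needs about 65. So the calculation is a two-sided paired t-test with one difference per patient.

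**2. Looking for that test among the listed analyses.**

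| Analysis | Question | Unit | Is it the sized test? |
|---|---|---|---|
| Item i, t and Wilcoxon tests | Which regions changed between time points | Observations within one participant | No |
| Item i, mixed model | Does SPECT change follow local dose | Regions and visits nested in patients | No |
| Item ii | As item i, by structure | As item i | No |
| Item iii | Model relating regional dose to GFR, with an F-test of fit | Model fit | No |
| Item iv | NTCP and EUD model fits | Model fit | No |

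None takes one SPECT value per patient and compares baseline with follow-up across patients.

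**3. Can the power of the mixed model be computed?** It would need a dose slope or correlation worth detecting, the number of regions per patient, the within-patient correlation and the residual variance. The article gives none of these.

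To show how far the answer depends on them, take a simple design-effect approximation with assumed inputs: m regions in each of 30 patients, intraclass correlation ρ, effective n = 30m/(1 + (m − 1)ρ), and detectable r = tanh(2.802/√(effective n − 3)).

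- m = 50, ρ = 0.05: effective n = 1500/3.45 = 434.8, r = 0.13.
- m = 10, ρ = 0.05: effective n = 300/1.45 = 206.9, r = 0.19.
- m = 50, ρ = 0.5: effective n = 1500/25.5 = 58.8, r = 0.36.
- m = 10, ρ = 0.5: effective n = 300/5.5 = 54.5, r = 0.37.

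The detectable correlation moves almost threefold over these assumptions. No single figure can be attributed to the plan.

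**The case against.** The case on the other side has four parts.

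- **The sizing section does not claim power for hypothesis 1.** It limits itself to a change in SPECT intensity. This is true, and it means the article makes no false statement about the dose correlation. It does not help with the other half of the point, because the change in intensity that was sized is not tested across patients in any listed analysis.
- **A repeated-measures model over all participants could supply a baseline-to-follow-up contrast.** It could, but the article gives the model's purpose as dose correlation and names no such contrast.
- **This is a condensed article, and a fuller plan may contain the test.** This is possible, so the point is confined to what the article lists. It is still a mismatch between two sections that the article chose to state, not a missing detail.
- **Feasibility also supports 30.** This stands. The sample size need not change; only the power statement is affected.

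A reader might go further and conclude that the study is underpowered for hypothesis 1. With one dose value and one response value per patient, Fisher's z gives tanh(2.802/√27) = 0.49 as the correlation detectable with 30 patients. The documents do not support that conclusion. The planned model uses local dose over many regions and several visits per patient, so 0.49 describes an analysis that is not planned. Nor should 30 be reduced to 24 for attrition: 30 is already the number of complete datasets, with up to 40 recruited to reach it.

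**Conclusion.** The point holds as a mismatch between sizing and analysis. The 80% (79.4% for a 10.5% fall with 30 patients, two-sided, SD of the paired difference 20%) belongs to a patient-level paired t-test that the article does not list. It applies neither to the within-participant tests nor to the mixed model.

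The power of the mixed model is unknown, not shown to be low. With many regions per patient and wide dose variation within kidneys it may be adequate.

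A reader might also infer that a group-level fall would never be reported. That goes too far: the article collects the SPECT change from baseline at all five follow-up visits and exports whole-kidney data, so such a summary could easily appear. It is simply not specified as the test that the power figure describes.

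**What to change.** 1. **Data analysis, item i.** Add one pre-specified SPECT summary per patient: mean normalised intensity over a kidney volume fixed in advance. Compare it between baseline and one named follow-up visit by a paired t-test across patients. The visit has to be named because there are five, and the calculation covers a single comparison.
2. **Statistical considerations.** State that the 80% applies to that test only. Then either say that the dose-correlation model was not formally powered, or give its detectable dose slope under stated assumptions on the number of regions per patient and the within-patient correlation. A patient-level correlation of 0.49 should not be given as the figure for hypothesis 1.

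The cost is one extra summary analysis on data already collected, a few reworded sentences and a less favourable power statement. No more patients are needed.

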### Data analysis

To correlate the patterns of change in SPECT signal with time relative to delivered dose distributions, SPECT signal intensity will be used as a measure of local renal function – a change in this measure is an indication of ‘renal response’. This response needs to be correlated with regional radiation dose distribution. Planned 3D radiation dose distributions will be digitally registered with kidney functional changes in order to generate dose response models. The planning CT will be registered to the initial SPECT/CT data for definition of baseline kidney location and function. Subsequent SPECT/CT data (intensity-normalised according to administered nuclide activity) will be registered both using bone anatomy as well as SPECT intensity distribution providing registration of radiation dose distribution and SPECT signal. All imaging shall be performed with the patient in the same position on a flat-topped couch, allowing quantification of changes in kidney positioning in the abdomen relative to the planned dose distribution. Co-registrations will be made using the Velocity AI software [24]. Velocity’s deformable image registration will allow subsequent SPECT images to be deformable registered to the baseline SPECT/CT, on the basis of both CT anatomy and SPECT signal, and for all co-registered data sets to be deformable registered to the planned 3D dose distribution. This will allow subsequent SPECT images to be deformable registered to the baseline SPECT/CT, on the basis of both CT anatomy and SPECT signal, and all co-registered data sets to be deformable registered to the planned 3D dose distribution (or vice-versa), exported from the Treatment Planning System in DICOM-RT format. Applying these methods to data collected during the RAPRASI study will allow accurate spatial registration of regional changes in SPECT signal to planned radiotherapy dose. The method of registration to obtain correlated SPECT/dose is shown on Figure 2.

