## Background

Radiotherapy has a significant role to play in the management of cancers of the upper abdomen, but high dose radiotherapy has been considerably limited by potential adverse normal tissue responses, in particular that of the kidneys. Because of their proximity to organs such as the pancreas, stomach and oesophagus, incidental radiation dose to the kidneys is frequently unavoidable when planning radiotherapy treatment. Our current understanding of kidney dose response and tolerance to radiation is rudimentary. This limits the delivery of a higher dose to the tumour and also the introduction and optimisation of new techniques to treat these upper gastrointestinal cancers, such as intensity modulated radiation therapy (IMRT).

Until recently, estimation of radiation-induced kidney damage was based on analysis of very basic radiotherapy data by Emami et al [1]. The Quantitative Analyses of Normal Tissue Effects in the Clinic (QUANTEC) review collated results of relevant studies that have been undertaken so far [2]. There have been previous key studies that have addressed the effects of partial kidney irradiation. In 1973, Thompson et al [3] reported the occurrence of clinical kidney toxicity several years after radiotherapy. Willet et al [4] found a dependence on the percentage of the volume being irradiated with a decrease in creatinine clearance. More recently, Kost et al [5] in 2002, used sequential scintigraphy to assess impairment of renal function and correlated it with the radiation dose distribution. Jansen et al [6] observed a progressive decrease in renal function in gastric cancer patients after postoperative radiotherapy. Studies in pigs [7,8] have shown that the response is dependent on whether one or both kidneys are irradiated and that the functional response depends on the compensatory response of the non-irradiated kidney.

A review of the preceding studies and the QUANTEC report [2] has highlighted several key points which have influenced the design of the RAPRASI study protocol:

– Kidneys have a late response to radiation (between 3 and 18 months).

– The functional response is dependent on the percentage of the kidney volume being irradiated and the dual nature of this organ influences their response.

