### Data collection and quality assurance

This study will be conducted according to the Human Research Ethics Committee (HREC)-approved study protocol and the ‘Note for Guidance on Good Clinical Practice (CPMP/ICH/135/95) annotated with TGA comments’ (Therapeutic Goods Administration DSEB July [18]. The study will be performed in accordance with the NHMRC ‘National Statement on Ethical Conduct in Human Research’ (© Commonwealth of Australia 2007) and the ethical principles within the ‘Declaration of Helsinki’ (Revised 1996) [19].

Sir Charles Gairdner Hospital will act as the sponsor of this study at both the Peter MacCallum Cancer Centre and Sir Charles Gairdner Hospital in Perth, Western Australia. Standard medical care (prophylactic, diagnostic and therapeutic procedures) remains the responsibility of the patient’s treating physician.

The investigator is responsible for ensuring that no participant undergoes any study related examination or investigations prior to obtaining written informed consent. The investigator will explain the aims, methods, possible benefits and potential hazards before the participant gives consent. The participant will be given sufficient time to read the documentation, understand the project and have any questions addressed prior to signing the consent form. The participants will be advised that they have the right to withdraw their consent to participate at any time without any consequences.

Participant confidentiality will be protected at all times. In any resulting publication or presentation, no patients will be identified.

Records will be retained for 15 years post study completion in a locked facility, in accordance with TGA requirements. Access to participant study records will be limited to treating clinician, chief investigator, his/her nominated co-investigators and the local study co-ordinators.

Collation of data will yield the following for each participant:

– Local kidney function/response to therapy: regional change in SPECT signal intensity:

•from baseline to 4 weeks post start of radiotherapy

•from baseline to 12 weeks post start of radiotherapy

•from baseline to 26 weeks post start of radiotherapy

•from baseline to 52 weeks post start of radiotherapy

•from baseline to 78 weeks post start of radiotherapy

– Planned 3D Regional radiation dose distributions intended to be experienced during radiation treatment.

– Kidney function measure: GFR at baseline, 4, 12, 26, 52 and 78 weeks.

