– Indication of existing and acquired co-morbidities.

– Information on adjuvant treatments.

GFR measurements using the ^51^Cr-EDTA clearance and Digital Imaging and Communication in Medicine (DICOM) formatted SPECT/CT images will be obtained on Siemens Symbia T6 SPECT/CT scanners located in the Department of Nuclear Medicine at SCGH and the Centre for Molecular Imaging at the PMCC. These images involve pre-injection of approximately 185 MBq of ^99m^Tc-DMSA (Radpharm DMS 1987/1), providing 128x128 pixel attenuation-corrected images reconstructed at approximately 5 mm pixel resolution. SPECT images are automatically registered to CT taken on the same device (6 slice helical CT scanner), with image settings sufficient for organ definition and bone matching with minimal radiation dose (typically 130 kV, 80-100 mA, 5 mm slice thickness). SPECT pixel intensity values will be normalised according to calibration images obtained on the scanner during monthly quality-assurance checks. SPECT data will be reconstructed using an ordered subset expectation maximization (OSEM) algorithm incorporating CT attenuation data.

Treatment plan data (images, structures, beam definitions, dose-volume data, and 3D dose distribution) will be exported in DICOM-RT format from the Treatment Planning System. (CMS XiO at SCGH, Varian Eclipse at PeterMac). Digitally reconstructed radiographs (DRRs) will be generated indicating local bony anatomy (upper pelvis, spine, ribs) and the location of kidneys from the planning CT. Variation in kidney position relative to local bony anatomy is of the order of SPECT image resolution [20,21]. Patient localisation will initially be to external marks, with on-line positioning then corrected according to localisation images spatially matched to the DRRs. Localisation images will be obtained either with the Brainlab Exactrac system (6D patient positioning) [22] or the Varian On-Board Imaging system (3D positioning) [23]. Applied patient shifts will be recorded together with localisation images. Where possible, kidney position will be identified on the localisation images for comparison with planned kidney outlines, as per standard departmental practice.

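### Mean SPECT intensity after deformable registration measures uptake per unit volume, so functional change that occurs through loss or gain of kidney tissue volume is not counted

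*Protocol article*

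**What the plan says.** All references are to the protocol article.

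- **Measure.** Under Data analysis: "SPECT signal intensity will be used as a measure of local renal function". The list of collected data, under Data collection and quality assurance, has the matching item: "Local kidney function/response to therapy: regional change in SPECT signal intensity".
- **Alignment.** Data analysis plans for "subsequent SPECT images to be deformable registered to the baseline SPECT/CT, on the basis of both CT anatomy and SPECT signal". The registered sets are then deformably matched to the planned dose, or the dose to them.
- **Normalisation.** Follow-up SPECT is "intensity-normalised according to administered nuclide activity" (Data analysis). Data collection and quality assurance adds: "SPECT pixel intensity values will be normalised according to calibration images obtained on the scanner during monthly quality-assurance checks". Neither contains a volume term.
- **Statistic.** Analysis i divides each kidney uniformly on the common image and dose grid and uses paired tests to "determine regions with significantly different mean SPECT-signal intensities between time-points for each study participant". A mixed model then relates local dose to SPECT signal change. Analysis ii repeats this for anatomical regions, and analysis iv fits complication models to SPECT and GFR changes.
- **Anatomical change.** Kidney position is to be quantified. Kidney volume at follow-up is not among the listed data, although CT is acquired with SPECT at every visit.
- **Biology.** The Background places the kidney's response at 3 to 18 months and reports from pig studies that "the functional response depends on the compensatory response of the non-irradiated kidney".

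**The concern.** Attenuation-corrected SPECT intensity is a concentration: uptake per unit volume of tissue. The uptake of a kidney or region is that concentration multiplied by its volume. If follow-up intensity is carried through a deformation onto the baseline shape, a shrunken kidney is stretched back and an enlarged one compressed. The regional mean then reports concentration only. This is so whichever signal drives the registration. It is also so if the dose is warped to the SPECT instead, because a mean intensity leaves out volume in either frame.

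The study aims to map where function is lost or gained after partial kidney irradiation. If part of that change occurs through tissue volume, the SPECT responses in analyses i, ii and iv miss that part. GFR is measured independently of the warp, but it is a total for both kidneys and cannot show where the change occurred.

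**Working it through.** **1. The plan's own figures (Statistical considerations).** Inputs: 10% reduction, measurement error 20% (taken as the SD of the paired difference), alpha 0.05 (taken as two-sided), power 80%.

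- Normal approximation: n = (20 × (1.960 + 0.842) / 10)² = 31.4, so 32.
- Noncentral t: power is 79.5% at n = 33 and 80.8% at n = 34.
- At n = 30 the detectable reduction is 10.58%, against the stated 10.5%.

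The stated 33 and 10.5% reproduce within rounding. They are not in dispute, and the fix leaves them unchanged.

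**2. What the stated response measures.** Let V be the ratio of follow-up to baseline volume and c the ratio of uptake per unit volume.

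- Change in total uptake = V × c − 1.
- Change in mean intensity after an unscaled warp = c − 1.

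The documents give no value for V or c. All values below are assumptions chosen to show the range.

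| V | c | Mean intensity reads | Total uptake changes |
|---|---|---|---|
| 0.90 | 1.00 | 0% | −10% |
| 0.80 | 1.00 | 0% | −20% |
| 0.70 | 1.00 | 0% | −30% |
| 0.80 | 0.90 | −10% | 0.80 × 0.90 − 1 = −28% |
| 1.20 | 1.00 | 0% | +20% |
| 1.00 | 0.80 | −20% | −20% |
| 0.80 | 1.25 | +25% | 0% |

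The second row equals the 20% reduction that the plan calls clinically significant. The sixth row shows that loss through concentration alone is fully counted. The last row shows that the two measures can also part in the other direction.

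**3. Would the change be obvious on the images?** Shrinkage per dimension for a 20% volume loss is 1 − 0.8^(1/3) = 7.2%. For 10% and 30% it is 3.5% and 11.2%. On an assumed 110 mm kidney, 7.2% is about 8 mm, or fewer than two of the plan's 5 mm pixels.

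**4. Consequence for the paired test at n = 30, SD 20%.** With V = 0.80 and c = 1, the measured quantity does not change and the test rejects only at its 5% level. If the measured quantity itself fell by 20%, power would be 99.96%. With V = 0.80 and c = 0.90, the reading is −10% and power is 75%. These powers apply to mean intensity with the plan's SD. Total uptake would have its own error, which the documents do not give.

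**The case against.** The strongest objection is that this is a condensed article. How intensity is resampled through a deformation may be set out in the full protocol, and the co-registration diagram is not available. That stands as a limit: a volume scaling could exist. But the article does state the measure, the alignment, the statistic and the normalisations, and together these give a concentration response. The point rests on that stated method.

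The pipeline is also described loosely. Bone anatomy is used as well as deformable matching. Under bone alignment alone, a shrunken kidney would leave low-signal voxels at its former edge, which would read as loss. Imperfect registration and partial-volume effects would likewise give back some signal, by an amount that cannot be computed here.

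Uptake per unit tissue is a coherent local measure to set against local dose, and volume can be recovered from the CT at each visit. Both are true. They are reasons to keep mean intensity and add to it.

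A reader might infer three stronger things that the documents do not support:

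- **That the link to GFR in analysis iii is broken.** Analysis iii fits models from the dose distribution to GFR. Warped SPECT intensity is named neither as its input nor as its outcome.
- **That the dose-response is biased toward zero, most at 52 and 78 weeks.** Shrinkage at high dose and enlargement at low dose would flatten the slope. But the documents report neither, and the compensation they cite is a functional response.
- **That every SPECT response should be replaced by uptake scaled with the Jacobian determinant (the local volume factor of the deformation).** The registration is driven partly by the SPECT signal, so its deformation field may reflect uptake defects as well as anatomy. Multiplying by it could carry registration artefact into the response.

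**Conclusion.** The point holds as a limit of the stated measure. Followed as written, the plan compares mean uptake per unit volume after deformable registration, and change in function through tissue volume does not enter the SPECT responses of analyses i, ii and iv. The shortfall equals total-uptake change minus concentration change: for assumed volume losses of 10%, 20% and 30% at unchanged concentration, 10, 20 and 30 percentage points. Its actual size in this cohort is unknown. The conclusion assumes that the warp carries intensity across without volume scaling, as the article's wording implies. Loss expressed as lower concentration is still detected, and analysis iii and the sample size are not affected.

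**What to change.** Keep mean intensity as the voxel-level response. Add the following:

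1. For whole-kidney and large-region SPECT responses in analyses i, ii and iv, also analyse change in total uptake. This is the activity-normalised counts summed within CT-defined contours on the undeformed scan at each visit.
2. Report CT kidney volume at each visit as a component, so that concentration and volume changes can be seen separately.
3. If Jacobian scaling is used for sub-regions, take the deformation from CT anatomy alone and apply it to regions, not single voxels.
4. State in the analysis wording that mean intensity measures uptake per unit volume.

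The cost is contouring and analysis time on scans already planned, plus contour or deformation noise in the added response. No new scan or patient is needed.
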